## Abstract

**Background:**

Current guidelines recommend less aggressive target hemoglobin A1c (HbA1c) levels based on older age and lower life expectancy for older adults with diabetes. The effectiveness of electronic health record (EHR) clinical decision support (CDS) in promoting guideline adherence is undermined by alert fatigue and poor workflow integration. Integrating behavioral economics (BE) and CDS tools is a novel approach to improving adherence to guidelines while minimizing clinician burden.

**Methods:**

We will apply a systematic, user-centered design approach to incorporate BE “nudges” into a CDS module and will perform user testing in two “vanguard” sites. To accomplish this, we will conduct (1) semi-structured interviews with key informants (*n* = 8), (2) a 2-h, design-thinking workshop to derive and refine initial module ideas, and (3) semi-structured group interviews at each site with clinic leaders and clinicians to elicit feedback on three proposed nudge module components (navigator section, inbasket refill protocol, medication preference list). Detailed field notes will be summarized by module idea and usability theme for rapid iteration. Frequency of firing and user action taken will be assessed in the first month of implementation via EHR reporting to confirm that module components and related reporting are working as expected as well as assess utilization. To assess the utilization and feasibility of the new tools and generate estimates of clinician compliance with the Choosing Wisely guideline for diabetes management in older adults, a 6-month, single-arm pilot study of the BE-EHR module will be conducted in six outpatient primary care clinics.

**Discussion:**

We hypothesize that a low burden, user-centered approach to design will yield a BE-driven, CDS module with relatively high utilization by clinicians. The resulting module will establish a platform for exploring the ability of BE concepts embedded within the EHR to affect guideline adherence for other use cases.

**Electronic supplementary material:**

The online version of this article (10.1186/s40814-019-0403-z) contains supplementary material, which is available to authorized users.

## Background

Intensive glycemic control is of unclear benefit and carries increased risk for older adults (defined here as 76 years and older) with diabetes [1]. A number of randomized controlled trials, including the Action to Control Cardiovascular Risk in Diabetes (ACCORD) trial [1], the Action in Diabetes and Vascular Disease: Preterax and Diamicron Modified Release Controlled Evaluation (ADVANCE) trial [2], and the Veterans Affairs Diabetes Trial (VADT) [3], found that intensive glycemic control was not protective for macrovascular complications of diabetes including myocardial infarction or stroke. These trials demonstrate the potential for harm with tight glycemic control, notably increased risk of hypoglycemia [4], and a suggestion of increased all-cause mortality [1]. Older adults are particularly susceptible to harms related to hypoglycemia in diabetes, including emergent hospitalization and neurologic complications [5–9]. Intensive glycemic treatment may also lead to increased risk of polypharmacy and adverse medicine interactions for older adults with multiple chronic conditions [10].

### Choosing Wisely guideline for older adults with diabetes

Due to evidence that tight glycemic control in older adults with diabetes may be medically harmful, in 2013 (revised in 2015), the American Geriatrics Society (AGS) developed ten Choosing Wisely (CW) guidelines, of which the third guideline states the following: “Avoid using medications other than metformin to achieve hemoglobin HbA1c<7.5% in most older adults; moderate control is generally better.” [11] Specifically, this guideline incorporates the balance between the number of comorbidities and life expectancy of older adults to provide target ranges for glycemic goals. Reasonable targets include an HbA1c of 7.0–7.5% in healthy, older adults with long life expectancy; 7.5–8.0% for patients with moderate comorbidity and a life expectancy of less than 10 years; and 8.0–9.0% for patients with multiple comorbid conditions and a shorter life expectancy [4, 12].

These recommendations build on previous work categorizing older adults with diabetes into three clinical groups based on health status [13] and have been endorsed by numerous expert panels and guidelines [8, 14, 15]. The target ranges for glycemic control are similar to HbA1c values that have been associated with the best outcomes for older adults with comorbid conditions in observational or modeling studies [16–18]. The American Diabetes Association (ADA) and others have recommended similar health status categories related to HbA1c targets in older adults [8, 14, 15]. Although the ADA guidelines do not identify less aggressive targets for HbA1c [8], other societies, including AGS, recommend similar less aggressive thresholds for glycemic control [15, 19–21].

Despite the CW recommendations, a substantial number of older adults have intensive glycemic control that may not be necessary [22–24]. Additionally, older patients with intensive glycemic control generally do not undergo de-intensification of therapy, suggesting opportunity for improving appropriate care [25]. To combat this problem, the proposed study utilizes a unique approach: using behavioral economics via electronic health records to influence provider behavior with respect to diabetes care for older adults.

### Behavioral economics and the EHR

The field of behavioral economics (BE) combines principles from economics and psychology to recognize the limitations of the classical economic framework that views human decision-makers as purely rational actors [26]. In reality, humans are predictably irrational [27], making common decision errors that are explicable through a set of psychological principles, and are therefore *predictable*. Traits contributing to decision errors include loss aversion, anchoring, overweighting of small probabilities, present bias, regret aversion, sensitivity to defaults, and the power of social comparisons [28]. Once recognized, each of these decision errors can be harnessed and overcome, often in the form of gentle “nudges” that make a desired behavior more likely [29–32].

Meanwhile, electronic health records (EHRs) now dominate the landscape, influencing nearly every clinical decision, workflow, and order placed by health care providers. Clinical decision support (CDS) is the primary EHR tool for influencing clinical decision-making and promoting adherence to clinical guidelines. CDS is an effective tool for improving provider performance and patient outcomes [33, 34]. Moreover, best practices for maximizing CDS effectiveness have been identified [35, 36]. Successful CDS must deliver accurate information in the right clinical context at the point of care and must be integrated into the relevant provider’s workflow [37]. Large, systematic reviews of CDS have demonstrated a moderate ability to reduce morbidity, utilization, and costs [34, 38]. These modest improvements, however, are undermined by the well-documented problems of alert fatigue and poor workflow integration, which together blunt the potential of the EHR and CDS to improve healthcare outcomes [39].

Integrating behavioral economics strategies and electronic health records using various CDS tools is a novel approach to improving guideline adherence that also seeks to minimize negative impacts on clinical workflow and cognitive load. For example, Meeker et al. integrated three BE concepts (suggested alternatives, accountable justification, and peer comparisons) into the EHR at 50 primary care practices to significantly (~ 5–7%) reduce inappropriate antibiotic prescribing for upper respiratory infections [40]. New approaches like these are needed to complement the traditional alerts, reminders, and other CDS tools that disrupt clinical workflow, increase cognitive load, and stress the limited capacity of clinicians to rationally process and evaluate the diverse and competing demands on their attention. By leveraging the opportunity presented by the EHR to combine modalities and extend the power of BE, this project seeks to develop a scalable intervention to reduce overtreatment in older adults with diabetes with minimal negative impact on clinician workflow or cognitive workload.

The objective of this study is to develop and pilot test a scalable, EHR customization toolkit that applies behavioral economic insights to promote appropriate diabetes care in older adults based on the AGS’s CW guideline to reduce overtreatment for the benefit of older adults with diabetes.

## Methods/design

This study employs a pragmatic, user-centered approach as illustrated in Fig. 1 to achieve two aims: (1) develop new BE CDS modules to improve provider adherence to the CW guideline targeting overtreatment among older adults with diabetes and (2) test the effectiveness of these BE CDS modules in a naturalized, clinical setting.

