Clinical decisions in accordance with the CW guideline will be drafted and approved by clinical experts on the research team and will guide actions prompted by text and visuals in the CDS modules. Example clinical actions include switching a patient’s medication to metformin, reducing the dose, or removing the prescription of an alternative medication for patients with an HbA1c laboratory value too tightly controlled given their calculated life expectancy. Once the new module has stabilized within the vanguard sites (workflow issues are resolved and clinician usage is stable) (aim 1), the tool will be activated at the pilot sites (aim 2).

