### Aim 2: Pilot testing the BE-EHR modules (phase 3)

To assess the utilization and feasibility of the new tools and generate preliminary estimates of clinician compliance with the CW guideline, a 6-month, single-arm pilot study of the BE-EHR module will be conducted in six outpatient primary care clinics.

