#### Intervention

The BE CDS module will trigger for appropriate patients according to the logic built into the module based on the patient’s age, life expectancy (as calculated by the algorithm described above), and current/target HbA1c. Based on these characteristics, the CDS may, for example, leverage the behavioral economic principle of defaults and suggest metformin if appropriate. Otherwise, the CDS will suggest not adding a new prescription if the HbA1c is above the lower bound of the target HbA1c threshold among the three life expectancy categories (7.0% for healthy patients, 7.5% for those with moderate comorbidity, and 8.0% for those with a shorter life expectancy [4, 12]). The CDS will suggest stopping or reducing the medication dose if the HbA1c is below the lower bound of the target HbA1c target threshold per life expectancy category, as that would indicate the patient’s HbA1c is being too tightly controlled. The BE CDS module (see Table 1) will be activated at the system level for all relevant diabetes EHR components. For example, a diabetes order set tailored to older adults might have default medications updated to be metformin and to reflect the CW-recommended glycemic targets for calculated life expectancy.

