#### Outcomes

Pilot study outcomes will measure implementation as well as provide initial estimates of the BE-EHR modules’ effectiveness.

Process outcomes include utilization, measured via the EHR, such as the percentage of alerts in which the clinician changes the default option. Other outcomes are noted in Table 1. We will also collect qualitative user feedback using user research methods deemed most appropriate (see Table 2) to understand clinicians’ experience with the BE-EHR module and evaluate the specific nudges, as well as explore acceptability, implementation, and adoption issues surrounding them, including assessing their impact on guideline-focused care for older adults with diabetes.

The primary clinical outcome is the percent of eligible patients who are compliant with the AGS CW guideline targeting overtreatment of older adults with diabetes. For each patient, the HbA1c level, diabetes medication prescription status, and life expectancy status will be determined. All patients whose HbA1c are within the target range for their life expectancy status will be considered compliant. Those whose HbA1c are below the target range and who are being treated with a non-metformin agent (i.e., are over-controlled) will be deemed non-compliant. If an eligible patient is on metformin only but the HbA1c is below the upper board of the target range, they will also be deemed non-compliant. These situations are delineated in Table 4. Patient-level compliance outcomes will be aggregated to produce a provider-level compliance rate as a proportion of each provider’s eligible patients.

**Table 4 Tab4:** Choosing Wisely non-compliance categories

Measured HbA1c	Patient category	Current prescription
< 7	Healthy	Non-metformin agent
< 7	Moderate comorbidity	Non-metformin agent
< 7	Shorter life expectancy	Non-metformin agent
7–7.5	Moderate comorbidity	Non-metformin agent
7–7.5	Shorter life expectancy	Non-metformin agent
7.5–8	Shorter life expectancy	Non-metformin agent

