### Limitations

As with any study design, there exist some limitations. First, the sample size that would be required to adequately power the present study is beyond the scope of this work. Hence, results from this pilot study will influence the decision of whether to push forward with a fully developed randomized controlled trial using only those nudges that show promise. Furthermore, with the incorporation of nudges (see Table 1) simultaneously across the EHR, it will be challenging to determine exactly which BE strategy or intervention has the strongest impact. Care will be taken to perform statistical analyses using adjustments and gathering summary statistics for different groups of nudges that are less likely to co-occur. Furthermore, we will collect information longitudinally to assess the order and timing with which clinicians were exposed to various nudges. As a pragmatic study, however, we are testing effectiveness in a real-world setting, for which clinicians in practice will be exposed to multiple nudges in combination or simultaneously, making the present design useful for assessing the overall impact in the EHR.

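### Aim 2 claims effectiveness and impact, but the primary clinical outcome is analysed as a single-arm compliance rate with no comparison, so it describes a level and not an effect

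*Protocol article*

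**What the plan says.** All references are to the protocol article.

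**Claims of effect.** Methods/design sets the second aim as to "test the effectiveness of these BE CDS modules in a naturalized, clinical setting". Outcomes says the pilot will "provide initial estimates of the BE-EHR modules’ effectiveness". Limitations describes the study as testing effectiveness under real-world conditions, "making the present design useful for assessing the overall impact in the EHR". The Summary again speaks of determining impact on adherence.

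**A narrower statement of purpose.** The section on Aim 2 puts it more modestly: "To assess the utilization and feasibility of the new tools and generate preliminary estimates of clinician compliance with the CW guideline".

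**Design.** In the same sentence: "a 6-month, single-arm pilot study of the BE-EHR module will be conducted in six outpatient primary care clinics".

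**Primary clinical outcome and its analysis.** Outcomes defines it as the percentage of eligible patients who comply with the guideline. Utilization rates, under Statistical methods and analysis, averages the patient indicator within each provider and summarises the provider rates with 95% confidence intervals. Neither section names a baseline period, control clinics, a reference rate or a change.

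**The one before-after measure.** In Table 1, the anchoring row (revised HbA1c laboratory reports) lists compliance before and after the update, in the column of utilization measures. Table 1 is introduced as a set of examples.

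**Where the tool is switched on.** The section on development of algorithms activates it at the pilot sites once it is stable in the vanguard sites. The Intervention section says that the module "will be activated at the system level for all relevant diabetes EHR components".

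**The concern.** An effect is a contrast between what happened with the module and what would have happened without it. The stated analysis supplies only the first part. The confidence interval around a compliance rate expresses sampling error in that rate and carries no information about whether the module changed it.

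Two things are at stake. First, a compliance rate reported under an aim worded as a test of effectiveness invites readers to credit the module with whatever level is found. Second, the pilot is meant to inform the decision on a randomized trial and to refine its design. That trial needs a compliance rate under usual care, and a rate measured only with the module active does not provide one.

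Limitations concedes that the study is not powered and that individual nudges will be hard to separate. It does not concede the lack of a comparator, and it says that the design suits assessment of overall impact.

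**Working it through.** The document states no sample size, effect size or baseline compliance rate, so there is no figure to reproduce. The check has three steps.

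**1. Claim against analysis**

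| Quantity | Needed for an effect | Stated in the plan |
|---|---|---|
| Compliance with the module active, p1 | yes | yes: provider-level rates with 95% CI |
| Compliance without it, p0 (earlier period, other clinics or reference value) | yes | not for the primary outcome; a before-after percentage for one example nudge in Table 1 |
| Contrast p1 − p0 with its uncertainty | yes | no |

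The Table 1 row does not fill the gap. It concerns one example component, it is listed as a utilization measure, and the analysis of compliance does not take it up. The laboratory report is also not among the three proposed components named in the abstract (navigator section, inbasket refill protocol, medication preference list).

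**2. What the rate alone implies**

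Effect = p1 − p0. Assume p1 = 60%, for illustration.

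- p0 = 50%: 60 − 50 = +10 points
- p0 = 60%: 60 − 60 = 0 points
- p0 = 70%: 60 − 70 = −10 points

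More patients would narrow the interval around p1 and leave this range unchanged. The gap is therefore one of identification and not of power.

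**3. What a before-after contrast could deliver (illustration)**

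Inputs from Table 3: 5187 patients in 78 practices, so 5187/78 = 66.5 per practice. The abstract and Aim 2 say six clinics, and Setting and population says four, so both are shown: n = 4 × 66.5 = 266 or 6 × 66.5 = 399. Assumptions: p = 0.5 in both periods, the same n in each period, periods treated as independent, 10 patients per provider, and an intraclass correlation of 0 or 0.05. The design effect at 0.05 is 1 + (10 − 1) × 0.05 = 1.45.

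- One rate, half-width 1.96 × √(0.25/n): 6.0 points (n = 266) or 4.9 points (n = 399).
- Pre-to-post difference, half-width 1.96 × √(0.5/n): 8.5 or 6.9 points.
- The same difference with clustering, 1.96 × √(0.5 × 1.45/n): 10.2 or 8.4 points.

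The same providers and many of the same patients would appear in both periods, which would tend to narrow the interval for the difference. The practice average is approximate: Table 3 includes endocrine practices and counts patients from age 75, while eligibility starts at 76. For scale only, the Background cites a reduction of about 5–7% for EHR nudges on antibiotic prescribing, which is a different outcome.

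**The case against.** The strongest reply is that this is an openly single-arm feasibility pilot. The abstract and the Aim 2 section state modest goals, Limitations disclaims power and defers to a randomized trial, and the pruning rule rests on utilization above 30% plus user feedback, not on a compliance effect. The article names no time window for the compliance rate and mentions longitudinal data and adjusted analyses. A baseline extract could be described in a fuller document that is not shown.

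Much of this stands. Utilization rates can be validly estimated in one arm, the pruning rule works without a contrast, and a single-arm pilot is a legitimate choice. It does not remove the mismatch. The article itself states the aim, the design, the primary outcome and the analysis, and these do not fit together. The longitudinal data and adjustments in Limitations are meant to separate nudges from one another, not to compare with care before activation.

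A reader might infer more than the documents support:

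- **That the pilot analyses nothing but compliance, or contains no before-after measure at all.** It also analyses utilization and user feedback, and Table 1 has the anchoring row.
- **That regression to the mean will produce a spurious improvement.** That would require following patients selected for low HbA1c. The stated outcome covers all eligible patients.
- **That every practice outside the pilot is a ready control.** The 78 practices include an unstated number of endocrine practices, and the two vanguard sites are exposed before the pilot.
- **That the tool will be switched on throughout the health system.** The Intervention wording can equally refer to which EHR components are changed. It is an ambiguity to be cleared up, not a proven conflict.

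**Conclusion.** The point holds for the primary clinical outcome. Followed as written, the plan yields utilization rates and a descriptive compliance level under the module. It does not yield an estimate of effectiveness or impact, and it leaves the later trial without a usual-care compliance rate. The Aim 2 section describes what the design can deliver; Methods/design, Outcomes, Limitations and the Summary go beyond it.

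The conclusion rests on the text of the article and needs no numerical assumption. The 60% example and the half-widths are illustrations under the assumptions given. They show that the compliance rate alone leaves even the direction of the effect open, and that a simple before-after estimate would carry a half-width of roughly 7 to 10 points. That is useful for planning a trial but imprecise beside an effect of a few points.

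**What to change.** Preferred change:

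1. Define a pre-activation period and extract the same Table 4 compliance outcome from the EHR for all eligible patients in the pilot clinics, in that period and in the pilot period. Use all eligible patients in both periods, not patients flagged by the module.
2. Apply the same life-expectancy look-back in both periods. The section on algorithms warns that recorded comorbidity depends on length of registration and frequency of visits. A longer look-back in the later period could move patients to higher HbA1c targets and lower apparent compliance with no change in practice.
3. Report the pre-to-post change with confidence intervals that account for clustering by provider or clinic, and report the pre-activation rate itself for planning the trial.
4. Where feasible, add unexposed primary care practices as a concurrent comparison to address time trends. A month-by-month comparison across all non-pilot practices is optional.
5. Reconcile the algorithm and Intervention sections on where the tool is activated.

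If no comparison is added, replace the effectiveness and impact wording in Methods/design, Outcomes, Limitations and the Summary with the terms of the Aim 2 section: utilization, feasibility and preliminary compliance estimates.

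The cost is a modest extra EHR query, including a run of the life-expectancy algorithm on the earlier period, and a simple clustered analysis. No patients or visits are added. The estimate remains non-randomized and imprecise, and should be labelled so. The rewording alone costs only text.
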